# VIII. Observation of adverse events

Adverse event (AE), refers to all adverse medical events that occur after a subject receives a test drug, which can be manifested as symptoms signs, diseases, or abnormalities in laboratory tests, but are not necessarily causally related to the test drug.

Serious Adverse Event (SAE) means an adverse medical event involving death, life-threatening, permanent or serious disability or loss of function, hospitalization or prolonged hospitalization of the subject, congenital anomalies, or birth defects that occurs after the subject receives the investigational drug.

Adverse drug reaction (ADR), any harmful or undesired reaction that occurs in a clinical trial that may be related to the medicinal product being tested. There is at least a reasonable possibility of a causal relationship between the trial medicinal product and the adverse event, i.e. correlation cannot be ruled out.

Suspected and Unexpected Serious Adverse Reaction (SUSAR), a suspected and unanticipated serious adverse reaction where the nature and severity of the clinical presentation exceeds the information available in the investigator's brochure for the test drug product, the specification of the marketed drug product, or the summary of product characteristics.

Subjects will be closely observed by the investigator and all adverse events reported by the subject or observed by the investigator from the time of randomization to the end of the study or early withdrawal from the study must be documented in the medical record or CRF, including laboratory and ancillary investigations, and should include, at a minimum, the name of the AE, the time of onset, time of termination, the severity, the presence or absence of corrective therapy, regression, and causal relationship to the study. causality, etc.

Changes in the subject's vital signs, physical examination, clinical presentation, and laboratory tests should be evaluated during the study. At the time of signing the informed consent form, the name and telephone number of an investigator whom the subject can contact in case of an emergency, or report of any medical symptoms, or occurrence of a subject-related AE must be provided.

Toxic reactions or AEs that existed prior to the subject's participation in the clinical study were recorded as AEs only if the grading was found to have increased by one or more grades from the baseline assessment during the study.

Adverse event description:

# Quality control and quality assurance of the study

(1) Adequate communication with patients participating in the trial study so that they understand the risks of the trial and obtain their informed consent and cooperation; (2) All applications of ultrasound in the trial were completed by a doctor with relevant qualifications; (3) The tube placement operation part of the trial was completed by a nurse with relevant qualifications; (4) The case collection form was designed in advance, and the researcher responsible for the collection of data was trained in the relevant knowledge to ensure the accuracy and timeliness of data (4) Design the case collection form in advance and train the researcher in charge of data collection to ensure the accuracy and timeliness of data collection.

# X. Data Safety Monitoring

A data safety monitoring program will be developed according to the risk level of the clinical study. All adverse events will be recorded in detail, appropriately handled and tracked until they are properly resolved or the condition is stabilized, and serious adverse events and unintended events will be reported to the Ethics Committee, the competent department, the sponsor and the drug regulatory authority in a timely manner in accordance with the regulations; the principal investigator will conduct a cumulative review of all adverse events on a regular basis, and convene a meeting of the investigators to assess the risks and benefits of the study when necessary; the double-blind trial will be able to Double-blind trials can be urgently unblinded when necessary to ensure the safety and rights of the subjects; independent data monitors will be arranged for studies with greater than minimal risk to monitor the study data at , and independent data safety monitoring committees will be set up for high-risk studies to monitor the cumulative safety and efficacy data in order to make a recommendation on whether to continue with the study or not.

# XI. Statistical Processing

1. Principles of statistical analysis

The statistical analysis of this trial will be carried out by statistical professionals who will be involved in the entire process from study design, statistical analysis of trial results, and ultimately the development of a statistical analysis plan prior to the locking of the study data in order to complete the statistical analysis report.

The software used for statistical analysis will be SAS version 9.4 or above. Statistical description and testing of data will be based on the characteristics of the data, and applicable descriptors and tests will be selected.

Quantitative data will be described using the number of cases, mean, standard deviation, median, upper quartile, lower quartile, minimum and maximum values; categorical data will be described by the number of cases and percentage of each category.

Comparisons of the general conditions of the two groups will be analyzed using appropriate methods according to the type of indicator; group comparisons of quantitative information will be made using the group t-test (chi-square, normal distribution) or Wilcoxon rank-sum test according to the distribution of the data (if the t-test is not applicable); categorical information will be analyzed using chi-square or exact probability (if the chi-square test is not applicable); and hierarchical information will be analyzed using the rank-sum test.

All statistical tests were two-sided, and a p-value less than or equal to 0.05 would be considered statistically significant for the differences tested (unless otherwise specified).

2. Baseline analysis

Baseline analysis was based on the full analysis set (FAS).

The number of enrolled and completed cases in the two groups at each center was summarized, with different dataset sizes, a list of specific shedding cases, and a comparison of shedding rates between the two groups. Subjects' basic demographic information (age, weight, etc.), medical and medication history were described and compared between the two balanced groups.

3. Effectiveness evaluation indexes

Validity evaluation is based on the Full Analysis Set (FAS) and the Compliance Program Set (PPS).

4. Main evaluation index

The primary evaluation metric is catheter tip localization accuracy.

5. Secondary evaluation indexes

The secondary evaluation indexes of this trial are catheterization time, confidence index of catheterization nurses and economy. In the comparison between the two groups, the t-test or Wilcoxon rank-sum test was used to measure the data according to the distribution of , and the chi-square test or Fisher's exact probability method was used to count the data.

6. Safety evaluation index

Safety evaluation was based on the safety analysis set (SS).

7. Adverse events

Adverse events, serious adverse events, device-related adverse events (or serious adverse events) that occurred during the study were described in terms of number of cases, number of cases, and incidence rate, and the specific manifestations, frequency, severity, and relevance to the device were described for all adverse events. Describe the type, number of cases, and incidence of device defects.

8. Vital signs

Statistical descriptions of changes in vital signs from baseline to post-treatment time points were performed for each group separately, including the number of subjects, mean, standard deviation, median, minimum, and maximum values. Measurement data were analyzed by group t-test or Wilcoxon rank-sum test, and count data were analyzed by two independent samples chi-square test or Fisher's exact probability method.

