**Produced by Gulou Hospital of Nanjing University School of Medicine**

**Programs Programs Abstract Summary**

| Project name | Accuracy study of trans-thoracic wall cardiac ultrasound (TTE) guided real-time localization of central venous catheter tip |
| --- | --- |
| Purpose of the study | a. To establish the technique of real-time positioning of catheter tip by cardiac ultrasound and optimize the operation procedure;  b. Conduct clinical studies to further investigate the consistency of trans-thoracic wall cardiac ultrasound localization of central venous catheter tip position and postoperative CT. |
| Study design | Diagnostic study |
| Total number of cases | 30 cases |
| Case selection | *Inclusion Criteria*  *Malignant tumors proposed for cyclic infusion of chemotherapeutic agents requiring placement of PICC, PORT catheter;*  *Patients aged >18 years old;*  *Agree to participate in this study and sign the informed consent for this study.* |
|  | *Exclusion criteria*  *Patients who cannot tolerate ultrasound monitoring after recent major chest surgery;*  *Patients who cannot tolerate CT examination;*  *Patients with contraindications to central venous catheter placement ;*  *Suffering from thrombophilia;*  *Those with abnormal coagulation function.* |
| Treatment Options | Those who signed the informed consent and met the inclusion and exclusion criteria were enrolled.  Patients requiring central venous catheterization  Undergoing TTE-guided catheterization |
| Evaluation of efficacy | *Indicators of effectiveness evaluation (primary and secondary outcome indicators)*   1. *Primary outcome indicators:*   *Precision of catheter tip localization (accuracy)*   1. *Secondary outcome indicators:*   *Surgical time, economy* |
|  | *Safety evaluation indicators*  *Incidence of surgical site infection, incidence of intraoperative adverse events, catheter ectasia* |
| Statistical methods | SPSS 20.0 statistical software was used to perform t-test, xo2 test and Fisher's exact test to analyze the safety, efficacy and economy. |
| Study period | 2023.04 to 2024.12 |

Table of Contents

[I. Background of the study 5](#_Toc110801521)

[Purpose of the Study 7](#_Toc110801522)

[III. Types of Study Design, Principles and Experimental Steps 7](#_Toc110801523)

[Case selection 9](#_Toc110801524)

[V. Research Methods and Technical Route 9](#_Toc110801525)

[Observation items and testing time point 12](#_Toc110801526)

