# III. Types of study design, principles and experimental steps

1. Study design

1. Type of study design: Diagnostic study
2. Research center: Nanjing Gulou Hospital Jiangbei Branch

2. Indications

Patients with malignant tumors requiring central venous catheterization for cyclic infusion of chemotherapy drugs; patients >18 years old; patients who agree to participate in the study and sign the informed consent form.

3. Endpoints

Patients' post-catheterization CT images.

4. Procedure

Patients sign an informed consent form

Screening

Failure

Withdrawal

Success

TTE is used to localize the catheter tip during catheterization.

Primary efficacy measures

Secondary efficacy measures

Safety evaluation

End of trial

Detection of catheter tip position by CT after catheterization

#

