# V. Research Methods and Technical Route

1. Subject enrollment

Patients were enrolled in the order of catheterization.

1. Intervention/Study drug name and specification

In this study, trans-thoracic wall cardiac ultrasound was used to locate the position of the catheter tip, all intraoperative ultrasound exploration steps were done by one doctor, tube placement steps were done by one nurse, and postoperative CT examination was performed in the imaging department of our hospital.

(1) Instruments

Ultrasonic instrument

(2) Methods

Ultrasound localization catheter tip operation procedure:

a. Patient position preparation: the patient takes a flat lying position, and the catheterization arm is placed at 90° to the torso;

b. Disinfecting and spreading the towel: measure the arm circumference, disinfect the catheter placement site, and spread the towel;

c. Placement of catheter: the catheterization nurse punctures the needle under ultrasound guidance and places the catheter;

d. Cardiac ultrasound-assisted catheter tip localization: ultrasound probe to explore the four-chambered heart section, observe the imaging effect (if the observation effect is not good, observe the short-axis section of the great arteries and subxiphoid section in turn), ultrasound doctor and the placement nurse to cooperate with the placement nurse to send the catheter until the doctor can observe the tip of the catheter under the ultrasound, retain the image to calculate the distance between the tip of the catheter and the septum at the end of cardiac contraction period, L, and the placement nurse to pull out the catheter to the outside. The catheterization nurse pulls the catheter outward for the length of L.

e. Proper fixation of the catheter: The placement nurse continues to complete the subsequent steps to properly fix the catheter.

3. Research intervention program

After patients signed the informed consent form, those who met the inclusion and exclusion criteria were enrolled;

Subjects received TTE-guided catheter placement, and the catheter tip position and procedure time were recorded during placement;

At the end of catheter placement, subjects had CT taken;

The patients were followed up postoperatively for the occurrence of complications (infections);

Analyzing whether there is consistency between TTE-guided catheter tip positioning and CT.

| Personnel Assignment | Assignment |
| --- | --- |

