| One physician | Responsible for the ultrasound localization part of the catheter placement process. |
| One catheterization nurse | Responsible for the catheterization process, cooperating with the doctor to complete the tip positioning. |
| One recorder | A recorder is responsible for recording data on site. |

4. Combination of drugs

This study does not involve the combination of drugs.

5. Research Flowchart

| Trial Flow Chart | | | |
| --- | --- | --- | --- |
| Window period  Trial Procedure | Visit 1  Screening period | Visit 2  Trial period | Visit 3  Observation Period |
|  | -1~0 days | 1 day | 2~ 3 days |
| Signed informed consent | × |  |  |
| Demographic information | × |  |  |
| Medical history and treatment history | × |  |  |
| Determination of inclusion/exclusion criteria | × |  |  |
| Randomization | × |  |  |
| Body temperature | × | × | × |
| Catheter placement |  | × |  |
| Observation and documentation of catheter tip position |  | × |  |
| CT examination |  |  | × |
| Complications | × | × | × |
| Adverse events |  | Continuous observation | |
| Surgical time |  | × |  |
| Nurse Confidence Index |  | × |  |
| Study Summary |  | × | |

6. Study-related laboratory tests

Blood tests (RBC/WBC/PLT/HBG) and coagulation tests (PT/APTT/FIB/D-Dimer/INR) will be completed during the screening period. During the trial and observation periods, if patients develop high fever and are reasonably suspected of having catheter-associated infections, blood cultures are required to confirm the diagnosis of catheter-associated infections.

7. Study-related imaging

Postoperative chest CT should be performed to confirm the location of the catheter tip under imaging.

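### Section XI prescribes between-group tests for a study with only one group; none of them can be run, and none gives usable inference for the primary proportion

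*Protocol*

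**What the plan says.** **The design.** Section III.1 gives "Type of study design: Diagnostic study" at one named centre, and the procedure scheme in III.4 is a single path from consent through TTE localisation to CT. The case selection section plans 30 subjects with no split, and removes after enrolment any patient in whom TTE was not used. Section V.1 says "Patients were enrolled in the order of catheterization", and V.3 has the subjects undergo TTE-guided placement followed by CT.

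**The analysis.** Section XI.1 sets out group t-tests, Wilcoxon rank-sum, chi-square and exact tests for comparing two groups. XI.2 says "The number of enrolled and completed cases in the two groups at each center was summarized", then adds a between-group comparison of dropout and a baseline comparison of two groups described as balanced. XI.5, on the secondary endpoints, says "In the comparison between the two groups, the t-test or Wilcoxon rank-sum test was used to measure the data", with chi-square or Fisher for counts. XI.8 assigns vital signs a group t-test or rank-sum test, and an independent-samples chi-square or Fisher test.

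**Randomisation.** The flow chart in V.5 has a row "Randomization" at the screening visit. Section VIII requires that adverse events "from the time of randomization to the end of the study or early withdrawal from the study must be documented".

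**The primary endpoint.** Section VII defines accuracy as the number of accurately placed cases divided by the total sample, read on CT. On its analysis, XI.4 says only "The primary evaluation metric is catheter tip localization accuracy"; XI.3 names the full analysis and per-protocol sets. The synopsis says "SPSS 20.0 statistical software was used to perform t-test", with chi-square and Fisher, for safety, efficacy and economy.

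**The concern.** The analysis text and the design text describe different studies. A two-sample test needs a second sample, and the protocol supplies none. This is more than detail deferred to an analysis plan. An analysis plan faithful to section XI could not be executed, and one faithful to the design would have to depart from the protocol's stated tests.

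Two things are at stake. First, the tests that the protocol offers for efficacy do nothing for the primary proportion. What remains usable in section XI is the general rule that categorical data are given as counts and percentages, while section II sets out to validate accuracy. Second, the secondary endpoints of surgical time and economy are assigned to a comparison that the study cannot make.

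**Working it through.** **Step 1. Is there a second group anywhere?** The possible candidates are:

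- Patients without TTE: removed after enrolment (case selection section), so they cannot act as controls.
- ECG-guided placement: appears in section VIII only as the fallback when a patient cannot tolerate probe pressure. It is not an arm.
- PICC versus PORT: catheter type is part of the eligibility wording. No section names it as a comparison.
- A second centre: section III names one.

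The number of comparison groups is therefore zero.

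**Step 2. What in section XI can be run with one group?**

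| Section XI item | Runs with one group? |
| --- | --- |
| Counts, means, SDs, quartiles, percentages (XI.1) | Yes |
| Enrolment and completion counts by centre (XI.2) | Yes, trivially, as one row |
| Between-group baseline and dropout comparisons (XI.1, XI.2) | No |
| Two-group tests on secondary endpoints (XI.5) | No |
| Adverse-event counts and incidences (XI.7) | Yes |
| Descriptive change in vital signs (XI.8) | Yes |
| Group and independent-samples tests on vital signs (XI.8) | No |

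**Step 3. Could a named test be read as a one-sample test for the primary endpoint?** A one-sample test of a proportion needs a reference value, and the protocol states none. The only external rate it quotes is a sensitivity of 98.6% in the background, which is not offered as a design value. No named test therefore applies to x/30.

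**Step 4. Is there a stated figure to reproduce?** The sample size of 30 comes without power, expected accuracy, precision or reference value, so there is nothing to reproduce. Nor does 30 look like a two-group size. Two groups of 15 with assumed rates of 98.6% and 80% would have about 37% power (normal approximation, rough at this size).

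**Step 5. What would inference suited to one group show?** The exact (Clopper-Pearson) 95% limits for x out of n are

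- lower = 0.025 quantile of Beta(x, n − x + 1)
- upper = 0.975 quantile of Beta(x + 1, n − x)

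At x = n the lower limit reduces to 0.025^(1/n), and 0.025^(1/30) = 0.884. The counts below are assumptions, because the protocol gives no expected accuracy.

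| x/30 | Estimate | Exact 95% CI |
| --- | --- | --- |
| 30/30 | 100% | 88.4 to 100% |
| 29/30 | 96.7% | 82.8 to 99.9% |
| 28/30 | 93.3% | 77.9 to 99.2% |
| 27/30 | 90.0% | 73.5 to 97.9% |
| 24/30 | 80.0% | 61.4 to 92.3% |

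**Step 6. Would the two-sided 0.05 rule have a use?** Only against a reference accuracy p0. Taking p0 as an assumption and using an exact upper-tail test at 0.025:

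- p0 = 0.80 needs at least 29/30 (tail probability 0.0105).
- p0 = 0.85 needs 30/30 (0.85^30 = 0.0076).
- p0 = 0.90 cannot be rejected by any result, since 0.90^30 = 0.042 exceeds 0.025.

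**Step 7. Randomisation and adverse-event recording.** In the flow chart, the randomisation row is marked at Visit 1 while adverse-event observation begins at Visit 2. Section VIII starts recording at randomisation. That event does not occur in this study, and even taken at face value the two places give different starts.

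**The case against.** The best defence is that section XI announces an analysis plan to be written before data lock, and that plan is not shown. A confidence-interval method for one proportion is commonly left to such a plan. The protocol does fix the quantity itself: section VII gives the definition, the formula and the CT reading, and section XI names the analysis sets. Section XI.1 also allows applicable descriptors and tests to be chosen. The two-group wording looks like carried-over template text, as does the remark on unblinding double-blind trials in section X. Conduct, data collection and descriptive output are unaffected.

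Much of this stands, and it limits what may be inferred:

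- A reader might infer that the absent interval is itself an error. It is not: alone, it could wait for the analysis plan.
- A reader might infer that section XI describes a randomised trial. It speaks of two groups and calls them balanced, but randomisation appears only in the flow chart and section VIII.
- A reader might infer that the whole analysis is unworkable. Step 2 shows otherwise.
- A reader might expect historical controls or a post-hoc split to be brought in. Nothing in the protocol proposes either, and no superiority hypothesis on time or economy is stated.
- The synopsis sentence names tests and software but no groups, so it does not by itself show a two-group plan.

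The contradiction survives. General latitude to choose suitable tests does not cancel explicit instructions to run two-group ones.

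**Conclusion.** The point holds as an internal contradiction that must be corrected. Every between-group test in section XI, covering general conditions, baseline, dropout, secondary endpoints and vital signs, lacks a second group, and the randomisation mentioned elsewhere has nothing to allocate. For the primary proportion, the named tests give no usable inference because there is neither a second group nor a reference value.

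This conclusion rests on the design text alone and needs no numerical assumption. The intervals do not measure the contradiction. They show how much uncertainty a bare percentage would hide, and they depend on assumed counts: the width is 24.4 percentage points at 27/30, and even 30/30 leaves accuracy below 90% possible.

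**What to change.** 1. Delete the two-group, multi-centre and dropout-comparison wording from XI.1, XI.2, XI.5 and XI.8, and the randomisation row from the flow chart. Bring the synopsis's list of tests into line.
2. State the primary analysis as x/n with an exact (Clopper-Pearson) or Wilson 95% confidence interval.
3. Summarise surgical time, cost and re-adjustments descriptively with 95% intervals.
4. Analyse change in body temperature, the only vital sign in the flow chart, within patient across the three scheduled visits.
5. Keep the two-sided 0.05 rule only if a reference accuracy is specified in advance.
6. Reconcile the start of adverse-event recording in section VIII with the flow chart, so that both refer to the same event and that event exists in this study.

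The cost is a change of wording, with no change to recruitment, procedures or data collected. The small downside is that the report will show a wide interval and will support no comparative claim on time or economy.
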